### Study participants

2.2

Participants in this study are consecutive patients admitted to the Fourth Hospital of Harbin Medical University in Harbin, Heilongjiang Province, China from March 2023 to March 2024 with differentiated thyroid cancer. We have begun recruiting study participants from March 2023, and each participant will begin the formal trial intervention after enrollment in the trial through face-to-face interactions at the hospital as well as signing the study informed consent form. Therefore, all patients are not recruited or starting the intervention at the same time, but will all complete the 3-month intervention cycle.

Inclusion criteria:

Patients are ≥18 years old.The patients are permanent residents of Heilongjiang Province (annual out-of-home time less than 1 month).The patients all met the relevant diagnostic criteria for thyroid cancer in the Guidelines for Diagnosis and Treatment of Thyroid Nodules and Differentiated Thyroid Cancer, and were diagnosed with differentiated thyroid cancer by pathological examination.Radiation iodine-131 therapy and endocrine therapy were given after radical surgery for thyroid cancer.The patient uses a smartphone on a daily basis and is familiar with the general function of WeChat.The patient voluntarily participates in the study and signs an informed consent form.

Exclusion criteria:

The patient has no fixed contact information, no family member is responsible for contacting the patient, and it is not convenient to contact the patient by phone or WeChat.The patient is taking any psychotropic drugs.The patient has mental symptoms such as delirium, slurred speech, uncooperative, etc.The patient has a combination of other serious systemic diseases, serious physical impairment and participation in other clinical trials.Pregnant or lactating women.Other reasons are not suitable to participate in the trial.

### Sample size

2.3

This study is a randomized controlled trial, the intervention group is the mHealth intervention group and the control group is the usual care group, the achievement rate of TSH in the study population is the main outcome indicator observed, and the patients’ TSH level control ﹤0.1 mU/L will be completed to achieve the standard. Based on the review of the literature, it is expected that the achievement rate of the mHealth intervention group is 90%, and the achievement rate of the control group is 60%. Setting bilateral *α* = 0.05, the degree of certainty was 90%. Using the PASS15 software, we obtained a sample size of N1 = 39 cases for the treatment group and N2 = 39 cases for the control group, and taking into account the loss of visits and refusal of visits by 20%, the final minimum number of subjects needed for the intervention group and the control group was 49 cases each, for a total of at least 98 subjects to be included in the study.

### Treatment programs

2.4

Patients in both groups will receive administration of iodine 131 therapy combined with thyroid hormone replacement therapy (53, 54). Prior to receiving iodine 131 therapy, patients will be required to undergo a thyroid uptake scan to determine if there is any residual or recurrent thyroid cancer (55). Depending on individual circumstances, patients are administered iodine 131 between 50 and 200 meters Curie (mCi) in a separate isolation room within the hospital. After administration, patients are hospitalized in an isolation room for 3 days to minimize radiation hazards, and are kept away from pregnant women and small children, avoiding close contact with other people, etc., to ensure safety. After iodine 131 treatment, start to take oral levothyroxine sodium tablets on the second natural day, generally the initial dose is 50 μg per day, the maximum amount does not exceed 100 μg, and the maintenance dose is 50–200 μg per day. Four weeks later, review the thyroid function index, and according to the results of the test, the dose will be maintained or adjusted. Therapeutic target: TSH 0.3 ~ 0.5 mU/L, free thyroxine (FT4) 10.3 ~ 25.8 pmol/L, free triiodothyronine (FT3) 2.16 ~ 6.78 pmol/L.

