### Outcomes

2.7

Primary Outcome: Change in TSH from Baseline and at 3 and 6 Months Follow-Up.

Secondary outcomes:

changes in self-management behaviors: changes measured by the MTM Theory Scale, changes in frequency of iodine-containing diets, medication adherence.Social cognitive and psychological: quality of life, satisfaction, depression, anxiety and fear of cancer recurrence.Metabolic control: thyroxine (T4), triiodothyronine (T3), FT3, FT4.

The corresponding study questionnaires completed by all patients at baseline as well as at follow-up were piggybacked on a web-based platform (Questionnaire Star). Clinical pharmacists distributed the questionnaires via Questionnaire Star, and patients were instructed to fill them out by pharmacists either face-to-face (during hospitalization) or by telephone (after discharge). Patient demographic information was collected through the case system and self-designed questionnaires.

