	The MTM theory scale	Questionnaire: Changes measured by the MTM Theory Scale	√	√	√
	Tthe frequency of iodine-containing diets	Questionnaire: Changes in the frequency of iodine-containing diets	√	√	√
	Medication adherence	Questionnaire: Medication Refill or Medication Adherence Scale (ARMS-7)	√	√	√
	Quality of life	Questionnaire: EuroQol-5 Dimensions 5 Levels(EQ-5D-5 L7)	√	√	√
	Satisfaction	Questionnaire: Customer Satisfaction Questionnaire (CSQ-3)	√	√	√
	Depression and anxiety	Questionnaire: Simplified version of the Anxiety Depression Scale (PHQ-4)	√	√	√
	Fear of cancer recurrence	Questionnaire: Fear of Cancer Recurrence Scale (FCR-4)	√	√	√

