### Questionnaires

2.9

Changes in self-management behaviors will be assessed by a self-designed MTM scale (57) consisting of 6 dimensions including PD, BC, CPE, ET, PC, and, CSE using a 5-point Likert scale design, the scale will be developed and final validation will be completed by the researcher, and 20 randomly selected participants who did not take part in the final trial will complete a pre-test from the recruited participants to determine the appearance validity and the content validity through pre-testing and expert testing to refine the model scale.

Changes in the frequency of iodine-containing diets will be assessed by patients through a self-administered the Iodine-containing Food Frequency Questionnaire (I-FFQ) questionnaire after adaptive adaptation and refinement based on the Food Frequency Questionnaire (FFQ) (58, 59). Preparation will be done in consultation with experts and based on food guidelines, several foods likely to be consumed on a daily basis with an iodine value greater than 400 mg/kg (60, 61), including iodized salt, will be selected as the target for measurement, and the time scale will be measured as the basis for frequency (62).

Medication adherence will be measured using the Renewal or Medication Adherence Scale (ARMS-7), which has seven entries and two dimensions: medication adherence (entries 1–4) and refills (entries 5–7), which is a 4-point Likert scale ranging from 1 (none) to 4 (all), notably one entry in the scale (the seventh) is reverse scored (1 = all to 4 = none). It measures self-reported medication adherence with respect to both taking medication as prescribed and taking medication as scheduled. The total score was derived by summing the responses to all items. The total score ranges between 7 and 28, with higher scores being associated with lower medication adherence. The scale has high validity and reliability in measuring medication adherence, with total scale item correlation coefficients ranging from 0.35 ~ 0.58 and a Cronbach’s alpha of 0.75 (63).

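### The 0 M visit is not placed relative to the first levothyroxine tablet, and sections 2.2 and 2.4 conflict on it, so change from baseline in TSH and adherence is a poorly defined and potentially very weak outcome

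*Protocol article*

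**What the plan says.** **Who is enrolled.** The inclusion criteria in section 2.2 of the protocol article are in the past tense: "Radiation iodine-131 therapy and endocrine therapy were given after radical surgery for thyroid cancer". The abstract and section 2.8 also describe patients already treated with iodine-131. Section 2.1.1 recruits patients who adhere well to treatment, which suggests treatment is under way. Section 2.4 is prospective: both groups will receive iodine-131 in hospital, stay in isolation for 3 days, and "After iodine 131 treatment, start to take oral levothyroxine sodium tablets on the second natural day", with thyroid function reviewed four weeks later.

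**What is measured.** Section 2.7 gives the primary outcome as change in TSH from baseline, at 3 and 6 months. Its first secondary group, changes in self-management behaviours, comprises "changes measured by the MTM Theory Scale, changes in frequency of iodine-containing diets, medication adherence". Table 2 schedules TSH and adherence ("Questionnaire: Medication Refill or Medication Adherence Scale (ARMS-7") at 0, 3 and 6 M. Section 2.9 divides the scale into "medication adherence (entries 1–4) and refills (entries 5–7".

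**How it is analysed.** Section 3 uses Mann–Whitney to compare baseline-to-endpoint change in scale scores between groups, and Wilcoxon for baseline against endpoint. Section 2.3 sizes the trial on a different quantity, the proportion with TSH below 0.1 mU/L: "it is expected that the achievement rate of the mHealth intervention group is 90%, and the achievement rate of the control group is 60" per cent.

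**The concern.** The start of levothyroxine can be expected to move both TSH and the answers to an adherence questionnaire, and 0 M is not fixed relative to it. If 0 M precedes the first tablet or follows it by days, the fall in TSH to 3 M is mostly the effect of starting the drug, and ARMS-7 has almost no course, and no refill, of that prescription to rate. If 0 M falls on established therapy, both baselines mean something else. If both kinds of patient enter, the change score mixes two quantities, and the 3 M and 6 M visits fall at different times on treatment.

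At stake are the listed primary outcome, the adherence part of the self-management objective, and the power of both comparisons. Who is enrolled and what baseline means belong in the protocol; they are not details to leave to an analysis plan.

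**Working it through.** **1. The plan's own figure.** Inputs from section 2.3: 90% v 60%; "Setting bilateral *α* = 0.05"; and "the degree of certainty was 90" per cent, read as power. Unpooled normal formula:

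n = (1.960 + 1.282)² × (0.9×0.1 + 0.6×0.4) / 0.3² = 38.53, so 39 per arm.

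39 / (1 − 0.20) = 48.75, so 49 per arm and 98 in total. The figures reproduce. They rest on a follow-up proportion, which needs no baseline, so the timing of 0 M does not affect them.

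**2. Does a common start-of-treatment shift bias the comparison?** Simulation with 39 per arm, 2,000 runs, normal outcomes, and a shift of 3 SD from baseline to follow-up in both arms (assumed).
- No intervention effect: Mann–Whitney on change rejects in about 5% of runs, so type I error holds. A Wilcoxon test within the control arm rejects in 100%.
- True effect of 0.75 SD: the mean between-arm difference in change stays at about 0.75.

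The shift therefore cancels between arms and dominates within them.

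**3. General cost in precision.** Let k be baseline SD over follow-up SD and ρ their correlation. Then Var(change)/Var(follow-up) = 1 + k² − 2ρk. Power is for the 0.75 SD effect in step 2; k and ρ are assumed.

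| k, ρ | Variance ratio | Power, change | Power, follow-up |
|---|---|---|---|
| 1, 0 | 1 + 1 − 0 = 2.0 | 61% | 89% |
| 1, 0.5 | 1 + 1 − 1 = 1.0 | 89% | 90% |
| 3, 0.2 | 1 + 9 − 1.2 = 8.8 | 18% | 89% |

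**4. TSH specifically.** The article gives no TSH distribution, so these inputs are assumptions: log-normal TSH; follow-up log-SD 1.2 with 90% v 60% below 0.1 mU/L; new-starter baseline median 10, 30 or 50 mU/L with log-SD 0.5; established-therapy baseline median 0.3 mU/L with log-SD 1.2; log-scale correlation 0 or 0.5; 39 per arm.

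Follow-up medians: 0.1 × exp(−1.2×1.2816) = 0.021 and 0.1 × exp(−1.2×0.2533) = 0.074 mU/L, a gap of about 0.05 mU/L. With a baseline median of 50, the baseline interquartile range is 50 × exp(±0.6745×0.5), about 36 to 70 mU/L. Raw change is then almost exactly minus the baseline, and the arm difference is swamped.

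Rejection rates (Mann–Whitney; repeat runs differ by a point or two):

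| Entrants | Raw change | Log change | Follow-up TSH |
|---|---|---|---|
| All new starters | 4–6% | 98% or more | 99% |
| Half and half | about 6% | 45–67% | 99% |
| All established | 18–22% | 86–99% | 99% |

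A test of the proportion below 0.1 mU/L rejects in 89–91% throughout, since it uses no baseline.

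**5. Adherence.** No arithmetic is needed. For a patient who starts levothyroxine under section 2.4 around 0 M, entries on taking and refilling have little or nothing from that course to describe. Under section 3 the score still enters the between-arm test as the subtracted term.

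**The case against.** The strongest reply is that no section puts baseline before the first tablet. The abstract and sections 2.1.1, 2.2 and 2.8 all point to patients already treated, and the future tense of section 2.4 may merely describe background care. Section 2.7 allows questionnaires in hospital or by telephone, and the 3-day isolation runs past the first tablet. No section describes a mixed cohort. This stands: a pre-levothyroxine baseline is an inference, and the defect is that the timing is open.

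A reader might go further and infer that the change measures the start of treatment rather than the programme, so that the comparison is invalid. Step 2 shows otherwise: that is true within an arm, not between randomised arms. A reader might also infer that a baseline ARMS-7 score cannot exist. The documents do not show that; the scale is not restricted to levothyroxine, and earlier post-surgical use is neither stated nor excluded.

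Three limits on the size also stand. Much of the loss on raw change comes from subtracting a skewed marker: it remains at 18–22% when everyone is on established therapy, and log change recovers nearly all the power if everyone is a new starter. Section 3 assigns Mann–Whitney to scale scores and names no test for TSH. The sizing endpoint is untouched.

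What remains is that sections 2.2 and 2.4 disagree, 0 M is not anchored, and section 2.7 nevertheless makes change from that point the primary outcome.

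**Conclusion.** The point holds as a problem of definition and efficiency, not of bias. As written, baseline TSH and ARMS-7 could be pre-treatment, within days of the start, or on established therapy. The randomised comparison stays valid under any of these. Within-arm changes would not be interpretable as programme effects, and a 0 M ARMS-7 score near the first tablet has no clear meaning for that course.

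Raw TSH change could have power between about 4% and 22%, against 99% for follow-up TSH and 89–91% for the status that sizes the trial. Log change avoids most of this except in a mixed cohort, where it falls to 45–67%. These figures rest on assumed TSH distributions. The low power of raw change persisted over assumed pre-treatment medians of 10 to 50 mU/L and correlations of 0 and 0.5. This should be corrected before analysis; it is not fatal to the trial.

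**What to change.** - Reconcile sections 2.2 and 2.4 on whether entrants have already had iodine-131 and levothyroxine, and define 0 M once relative to both. This is a matter of definition; no clinical rule is proposed.
- Compare arms on TSH at 3 M and 6 M, using either the below-0.1 mU/L status from section 2.3 or the follow-up value on a log or rank scale, not raw change from baseline.
- Compare ARMS-7 on the 3 M and 6 M scores, adjusting for the 0 M score only in patients already on levothyroxine at 0 M.
- If both kinds of patient enter, record time since levothyroxine start at entry and adjust for it.

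The cost is protocol wording and one recorded date, with no extra visits or patients. The downside is that change from baseline is no longer the headline result; it can still be reported descriptively.

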### Variables measurement

2.8

Socio-demographic variables will be collected: gender, age, education, usual residence, *per capita* monthly income of the family, mode of bearing medical expenses, and clinical information such as duration of DTC, detailed medical history.

Physiological Indicator Variables: TSH will be detected using radioimmunoassay (RIA), the medical staff will clean the patient’s blood collection site using a sterilized cotton ball, and then use a needle to take an appropriate amount of fasting venous blood 5 mL, centrifuged at 3000 r/min for 5 min, serum will be separated, and a certain amount of TSH antibody labeled with the radioisotope iodine-125 will be added to the processed serum to bind to the TSH to be detected. TSH. Using biochemical techniques, the antibody-bound TSH and unbound free TSH were separated into solid phase and free phase. The radioisotopes in the solid phase are measured to obtain a corresponding count value, from which the concentration of TSH in the sample can be determined. Based on the stratification of risk factors for recurrence of differentiated thyroid cancer, patients can be categorized into low-risk, intermediate-risk, and high-risk strata, and postoperative serum TSH target values are set accordingly (56). In general, the division is based on factors such as age, gender, tumor stage, presence of lymph node metastasis, and type of thyroid cancer variant. All patients included in this trial were high-risk patients treated with iodine 131, and according to treatment guidelines, for high-risk patients, postoperative serum TSH should be suppressed to very low levels (<0.1 mIU/L) or completely suppress thyroid function to minimize the risk of recurrence. Therefore, the TSH compliance rate was defined as postoperative serum TSH < 0.1 mU/L, and this criterion was used to calculate the TSH compliance rate.

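### Section 2.4 doses both arms toward TSH 0.3–0.5 mU/L, while sections 2.3 and 2.8 count success only below 0.1 mU/L

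*Protocol article*

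**What the plan says.** - **Dosing (section 2.4, Treatment programs).** The section covers both groups. Levothyroxine starts after iodine-131, thyroid function is reviewed four weeks later, and "according to the results of the test, the dose will be maintained or adjusted". The goal is then given as "Therapeutic target: TSH 0.3 ~ 0.5 mU/L", alongside ranges for FT4 and FT3.
- **Sizing (section 2.3, Sample size).** Here "the achievement rate of TSH in the study population is the main outcome indicator observed", with the standard met when TSH is below 0.1 mU/L. The expected rates are 90% with the intervention and 60% with control.
- **Measurement (section 2.8, Variables measurement).** The section states: "All patients included in this trial were high-risk patients treated with iodine 131". It says guidelines call for TSH below 0.1 mIU/L in such patients to limit recurrence, and concludes that "the TSH compliance rate was defined as postoperative serum TSH < 0.1 mU/L".
- **Outcomes (section 2.7).** The listed primary outcome is continuous: "Primary Outcome: Change in TSH from Baseline and at 3 and 6 Months Follow-Up". It carries no threshold.

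**The concern.** The treatment rule and the success rule pull in different directions, and nothing in the article limits 0.3–0.5 to a risk stratum or an early titration phase.

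Two things are at stake. The first is patient care. A patient whose TSH is already below 0.1 lies under the 2.4 target, so a clinician working to 2.4 would have reason to lower the dose, away from the level that 2.8 says the patient needs.

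The second is what the achievement rate measures. The intervention includes daily medication reminders and other support for adherence. Perfect adherence to a regimen titrated to 0.3–0.5 gives a TSH of 0.3–0.5, which is scored as failure. The rate would then no longer reward the behaviour that the intervention promotes, and the planned 90% and 60% would be hard to defend.

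**Working it through.** **1. Do the two rules overlap?** The dosing target is 0.3 to 0.5 mU/L (2.4). Success is below 0.1 mU/L (2.3, 2.8). The units mU/L and mIU/L are equivalent here. The intersection of [0.3, 0.5] and [0, 0.1) is empty, and 0.3 / 0.1 = 3. Every patient held at the dosing target is a non-achiever.

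**2. Does the stated sample size reproduce?** Inputs from 2.3: rates 0.90 and 0.60, two-sided α = 0.05, power 90%, loss 20%.

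Two-proportion formula with unpooled variance:

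n = (z₀.₉₇₅ + z₀.₉₀)² × [p₁(1−p₁) + p₂(1−p₂)] / (p₁−p₂)²

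= (1.960 + 1.282)² × (0.09 + 0.24) / 0.09 = 38.53 with unrounded quantiles, rounded up to 39.

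With loss: 39 / 0.8 = 48.75, rounded up to 49 per arm, 98 in total. Both figures match the protocol, so the arithmetic in 2.3 is sound.

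**3. What could the conflict cost in power?** The documents give no figure for how closely clinicians follow 2.4. Assumption: the same share s of would-be achievers in each arm is held at 0.3–0.5 and scored as failures. Then p₁ = 0.9(1−s), p₂ = 0.6(1−s), and with 39 analysed per arm

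power = Φ( (p₁−p₂) / √{[p₁(1−p₁) + p₂(1−p₂)] / 39} − 1.960 ).

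| s | Intervention | Control | Difference | Power, unpooled | Power, pooled |
|---|---|---|---|---|---|
| 0 | 90% | 60% | 30 points | 90% | 88% |
| 10% | 81% | 54% | 27 points | 76% | 73% |
| 25% | 67.5% | 45% | 22.5 points | 54% | 52% |
| 50% | 45% | 30% | 15 points | 28% | 27% |

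Worked line for s = 10%: 0.81×0.19 + 0.54×0.46 = 0.4023; √(0.4023/39) = 0.1016; 0.27/0.1016 = 2.658; Φ(2.658 − 1.960) = 0.76.

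Zero achievement in both arms is only the limiting case s = 100%.

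**4. What if the share differs between arms?** Losing 10% of achievers in control only gives 90% against 54%, a gap of 36 points. Losing 10% in the intervention arm only gives 81% against 60%, a gap of 21 points. The direction of the effect on the gap thus depends on the shares being similar.

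**The case against.** The contradiction is not in dispute, but its consequences can be argued down.

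- **The power loss rests on equal shares.** The intervention arm has more contact with physicians and nurses, so the share held at 0.3–0.5 could differ between arms in either direction, and step 4 shows that the gap could even widen. This stands as a limit: the power figures are illustrations and do not establish the finding.
- **The listed primary outcome is continuous.** Change in TSH in 2.7 has no cut-off, so it is not mis-scored. This also stands. The mis-scoring reaches the rate in 2.3 and 2.8. Still, that rate sizes the trial, and the continuous outcome is driven by the same titration target.
- **Section 2.4 prescribes no dose reduction below 0.3.** It says only that the dose is kept or changed on the results. That is fair: the lower dose is an inference. But 2.4 is the section that directs dosing, and a stated target is what the results are judged against.
- **The document alone does not prove which number is wrong.** Section 2.4 cites sources for the regimen that are not at hand. This is why the clinical lead must confirm. The balance favours below 0.1, which appears in two sections with a stated reason, whereas 0.3–0.5 appears once without one.

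**Conclusion.** The concern holds. As written, a clinician cannot satisfy both the dosing target and the success criterion in the same patient. This follows from the text and needs no assumption.

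How much it harms the trial depends on how far 2.4 is followed, which the documents do not say. If the affected share is equal in both arms, a share of 10% already takes power from 90% to 76%, and 25% takes it to 54%. With unequal shares the effect on the gap could go either way, but the 90% and 60% rates could not both be relied on. The planned 39 (49 with losses) per arm is correct for its stated inputs. This must be fixed, because it concerns the treatment target of enrolled cancer patients as well as the rate that sizes the trial.

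**What to change.** With confirmation from the clinical lead, change the TSH target in 2.4 to below 0.1 mU/L, so that 2.3, 2.4 and 2.8 state one target. When doing so, check that the FT4 and FT3 ranges and the dose limits in the same section still fit, and confirm that the literature behind the 90% and 60% rates used the below-0.1 criterion. If it did, the endpoint, the rates and the 49 per arm stay as they are.

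If the clinical lead instead confirms 0.3–0.5 as intended, change the success criterion in 2.3 and the definition and rationale in 2.8, and justify the 90% and 60% rates again for the new criterion. Stating the high-risk requirement among the inclusion criteria in 2.2 would help but is optional.

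**Cost.** The text change is small and adds no patients. It is nevertheless an amendment to a dosing target in a trial that has recruited since March 2023. It needs ethics approval or notification (section 3.1.4), and patients already titrated under 2.4 may need their dose reviewed.
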